### Interim analyses {21b}

In the event of frequent side effects, we will stop the intervention and present the results to the ethics committee of Mashhad University of Medical Sciences (MUMS) for further determination.

### Methods in analysis to handle protocol non-adherence and any statistical methods to handle missing data {20c}

To include the outcome data of the participants in the data analysis regardless of protocol adherence, all the analyses will be performed in agreement with the intention-to-treat principle. The last observation by the forward method will be used to impute the missing data for the intention-to-treat analysis.

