### Outcomes {12}

The primary outcome of the current trial is the measurement of the serum levels of fat-soluble vitamins once at the onset of enrollment and once at the end of the trial after 3 months.

The secondary outcomes are clinical criteria evaluation by the Shwachman-Kulczycki score (an index to evaluate the severity of the disease in CF patients, which includes general activity, physical examination, nutrition, and radiological findings), anthropometric assessment by the BMI *Z* score, and quality of life evaluation by using the CFQ (Health-Related Quality of Life in Children with Cystic Fibrosis) from the baseline to 3 months of the intervention (Fig. 1).

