### Participant timeline {13}

Nutritional suggestions will be given to all the patients and their parents and legal guardians based on the CF requirements and modifiable CREON dosing according to the level of dietary fat. Additionally, the patients or their parents completed the CFQ, depending on age.All anthropometric measurements (weight and height without shoes) will be performed under equal guidance using a digital scale (model: SECA).The primary and secondary outcomes of the treatment will be examined before and after 3 months of treatment. The clinical evaluation and follow-up will be carried out via monthly visits and phone calls with the patients.Approximately 6 mL of blood will be collected before and after 3 months from the beginning of the trial and centrifuged, with the serum separated from the sediment, and preserved at a minimum temperature of − 20 °C.

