### Sample size {14}

Due to the lack of clinical trials on the evaluation of the efficacy of nanomicelle formulation of fat-soluble vitamins in children with cystic fibrosis, we use the researcher’s experience to estimate the sample size. According to this, about 60% of CF patients who use the routine formulation of fat-soluble vitamins are treated for vitamin D deficiency. It is estimated that the new method will increase the recovery rate by 30–40%. Considering alpha = 0.05 and power = 80%, the minimum required sample size in each group is estimated to be 33 people. By considering the 10% dropout rate for the sample, a total of 37 samples for each group was calculated. In total, 74 patients with CF are needed to be included in the randomization aspect of this research.

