### Data management {19}

In the current trial, the database will be created from the questionnaire of clinical data and laboratory assay results in Excel software and SPSS. The trial researchers will collect the data at the beginning and during the follow-up and record the obtained data in the paper checklists as well as the designed Excel datasheet. Next, the data will be analyzed in SPSS. To ensure security, the login password is allowed only for the trial researchers. The database will only accept the variables that are consistent with the previous entries, and it could also be altered in the case of randomly missing values. Semimonthly, 10% of the electronic data will be randomly compared with the paper questionnaires.

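### With vitamins measured only at baseline and 3 months, last observation carried forward records zero change for every missing 3-month sample

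*Protocol article*

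**What the plan says.** Section {20c} of the protocol article commits to intention to treat ("all the analyses will be performed in agreement with the intention-to-treat principle") and names a single imputation rule: "The last observation by the forward method will be used to impute the missing data for the intention-to-treat analysis". It gives no alternative and no sensitivity analysis.

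The Outcomes section {12} fixes the timing of the primary outcome: "once at the onset of enrollment and once at the end of the trial after 3 months". The Participant timeline {13} agrees for the blood draws ("Approximately 6 mL of blood will be collected before and after 3 months from the beginning of the trial") and for all other outcomes ("The primary and secondary outcomes of the treatment will be examined before and after 3 months of treatment"). The monthly visits and phone calls serve clinical evaluation and follow-up; no vitamin level is taken at them.

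The Sample size section {14} starts from the premise that "about 60% of CF patients who use the routine formulation of fat-soluble vitamins are treated for vitamin D deficiency", expects the new form to raise recovery by 30-40%, obtains 33 per group for 80% power, and raises this to 37 per group (74 in total) for 10% dropout.

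**The concern.** Carrying a value forward presupposes a post-baseline value to carry. With two time points there is none, so the rule becomes baseline carried forward, and the imputed result is fixed before treatment starts.

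Two things are at stake. First, both arms receive vitamins. If levels move during the trial, a zero change is wrong for those who leave. Equal dropout then dilutes a true difference, and unequal dropout shifts the comparison. Unequal dropout is plausible: participants know their arm (section {17a}), and the Discussion describes one dose a day against four pills a day.

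Second, the step from 33 to 37 treats dropouts as lost and relies on 33 completers for the power. The imputation rule keeps the dropouts in the analysis as unchanged. The sample size and the analysis therefore make different assumptions about the same participants.

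**Working it through.** **Inputs from the protocol article.** Two measurement times ({12}, {13}); control recovery 60%, increase 30-40%, alpha 0.05, power 80%, 33 per group, 10% dropout, 37 per group ({14}). **Assumed, because the article does not give them:** a two-sided test, dropout split by arm, mean change in the control arm, and dropout unrelated to outcome.

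**1. The plan's own figure.** Reading the increase as 30 percentage points (60% v 90%), with pooled p = 0.75:

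n = [1.96 √(2 × 0.75 × 0.25) + 0.842 √(0.60 × 0.40 + 0.90 × 0.10)]² / 0.30² = 31.5, so 32 per group against 33 stated. Then 33 / 0.9 = 36.7, so 37 per group and 74 in total. A relative increase of 30-40% (78% or 84%) would need 103 or 54 per group, so the absolute reading is the one that fits. With 33 completers per group the power is 81.9%.

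**2. Equal dropout, recovery proportion.** A participant deficient at baseline whose baseline value is carried forward counts as not recovered. With 10% dropout:
- control 0.60 × 0.9 = 54%; nanomicelle 0.90 × 0.9 = 81%; difference 27 points instead of 30;
- power with 37 per group: Φ{[0.27 √37 − 1.96 √(2 × 0.675 × 0.325)] / √(0.54 × 0.46 + 0.81 × 0.19)} = 70.6% (71.4% by exact enumeration);
- 47 per group would be needed to restore 80%.

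**3. Equal dropout, serum level (change score).** Let the SD of change be 1, the dropout proportion q and an arm's mean change m. With zeros imputed, the arm mean becomes (1 − q)m and the variance (1 − q) + q(1 − q)m². Take a true difference of 0.70 SD, for which 33 completers per arm give about 80% power. With q = 0.10 the difference becomes 0.9 × 0.70 = 0.63 SD. With 37 per arm:

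| Control mean rise | Variance, nanomicelle / control | SE of difference | Power |
|---|---|---|---|
| 0 | 0.944 / 0.900 | 0.223 | about 80% |
| 0.5 SD | 1.030 / 0.923 | 0.230 | about 78% |
| 1 SD | 1.160 / 0.990 | 0.241 | 73-74% |

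**4. Unequal dropout, no true effect (change score).** With a common rise m, the spurious difference is m × (difference in dropout proportions). With 37 per arm:

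| Dropout split | Common rise | Bias | Type I error |
|---|---|---|---|
| 15% v 5% | 0 | 0 | about 5% |
| 15% v 5% | 0.5 SD | 0.05 SD | about 5.5% |
| 15% v 5% | 1 SD | 0.10 SD | about 7.3% |
| 20% v 5% | 1 SD | 0.15 SD | about 10% |

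The 15% v 5% split averages the plan's 10%. The 20% v 5% split averages 12.5%, so the last row goes beyond it.

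**5. Unequal dropout with a true effect, recovery proportion (60% v 90%).** Control 5%, nanomicelle 15%: 57% v 76.5%, difference 19.5 points, power 42.7%. Control 15%, nanomicelle 5%: 51% v 85.5%, difference 34.5 points, power 90.7%. The distortion can go either way.

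**The case against.** The strongest reply is that the harm may be small. Controls receive a formulation like their routine treatment, and the Background describes deficiency that persists despite CF vitamins. A control change near zero is therefore plausible. In that case power on change scores stays near 80%, and unequal dropout does not raise the type I error. With a milder split of 12% v 8%, type I error stays below 6% even for a 1 SD rise. The 71% figure concerns a recovery proportion that appears only in the sizing; section {20a} compares continuous variables by t-test or Mann-Whitney. It also assumes that every dropout was deficient at baseline, which the eligibility criteria do not require. All of this stands, and it is why the size is given as a range. Participants who stop treatment but still give the 3-month sample are not imputed at all.

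A reader might be tempted by four stronger statements that do not hold:
- **The standard errors are also wrong.** When this was simulated with dropout unrelated to outcome, the mean t-test standard error matched the true sampling SD (0.229 against 0.229). The excess type I error comes from bias in the mean difference.
- **The bias always favours the better-retained arm.** That requires levels to rise. The direction depends on which arm loses more participants and on which way levels move.
- **The dropout allowance is wholly undone.** On change scores with a stable control arm, almost nothing is lost.
- **The Data management section {19} contains a second, conflicting imputation rule.** Its remark that "it could also be altered in the case of randomly missing values" stands among data-entry checks. It is unclear, but it cannot be read with confidence as an imputation method.

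**Conclusion.** The point holds. It follows from the stated timing alone that the rule imputes the pre-treatment value for every missing 3-month sample. The article states this choice; it does not leave it to a separate analysis plan.

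The consequence runs from negligible to moderate at the plan's 10% dropout. A true difference is diluted by 10%. Power is between about 73% and 80% on change scores, and 71% on the recovery proportion if all dropouts were deficient at baseline, against the 80% stated. Type I error is about 5% to 7.3% at 15% v 5%, and reaches about 10% only if dropout is 20% v 5% and both arms rise by 1 SD. The dropout splits and mean rises are assumptions, since the article gives only the overall 10%. The case for change rests on an imputed value that carries no information about treatment, in the primary analysis, when a better method costs little.

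**What to change.** In section {20c}, replace carrying the last observation forward by:
- **Main analysis:** ANCOVA of the 3-month serum level on arm and baseline level, with multiple imputation by arm (baseline level, age, adherence) under missing at random, so that all randomised participants are included as intention to treat requires. Section {20a} already uses ANCOVA for the secondary outcomes; extend it there to the primary outcome.
- **Sensitivity analyses:** one under missing not at random, for example delta-adjusted imputation. Keep baseline carried forward at most as a further analysis, labelled as such.

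The step from 33 to 37 then matches the analysis, because dropouts no longer enter as unchanged.

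The cost is revised wording and a little more analysis work; no extra participants, visits or samples are needed. The downside is that the main analysis relies on missing at random, which the data cannot verify and which the sensitivity analysis is there to probe.

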**Table 2 Tab2:**
[figure not shown]
Schedule of enrolment, intervention, and assessment based in the Standard Protocol Items Recommendations for Interventional Trials (SPIRIT) guideline

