## Assignment of interventions: blinding

### Who will be blinded {17a}

Due to the distinguishable appearance of the drugs used in the intervention and control groups, both participants and the main researcher are aware of the group assignments for the patients. However, the data analyst and the nutritionist, responsible for regular communication through weekly phone calls and monthly in-person visits, are blinded to the trial details. In clinical trial studies, the term “blinded” typically applies to patient involvement. In this study, only the data analyst and the nutritionist, who assess patients, operate under blind conditions. Consequently, the trial is registered as “not blinded” in accordance with standard practices in clinical trial blinding.

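### Serum vitamins are measured only at baseline and 3 months, so carrying the last observation forward scores each missing 3-month level as no change

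*Protocol article*

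**What the plan says.** Section {20c} applies intention-to-treat to all analyses and names one rule for missing data: "The last observation by the forward method will be used to impute the missing data for the intention-to-treat analysis". The wording is awkward, but last observation carried forward is its only sensible reading.

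Section {12} measures the serum levels "once at the onset of enrollment and once at the end of the trial after 3 months". Section {13} agrees: "Approximately 6 mL of blood will be collected before and after 3 months from the beginning of the trial". Sections {12} and {13} also place the secondary outcomes (Shwachman-Kulczycki score, BMI Z score, CFQ) before treatment and at 3 months.

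There is contact in between. Section {13} says "The clinical evaluation and follow-up will be carried out via monthly visits and phone calls with the patients", and section {17a} describes a nutritionist "responsible for regular communication through weekly phone calls and monthly in-person visits". The text assigns no outcome measurement to these contacts. Table 2, captioned "Schedule of enrolment, intervention, and assessment based in the Standard Protocol Items Recommendations for Interventional Trials (SPIRIT) guideline", is not reproduced in the text available.

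On expected loss, section {14} says: "By considering the 10% dropout rate for the sample, a total of 37 samples for each group was calculated".

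**The concern.** Carry-forward is meant for repeated measurements, where a recent on-treatment value exists. Here no on-treatment vitamin level exists before 3 months, so the rule becomes baseline carried forward. A child with no 3-month sample enters the analysis as a child whose vitamin levels did not move.

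That is a doubtful default. The control arm takes standard vitamins and the intervention arm takes the nanomicelle drops, so children in either arm may gain. Inserting zeros pulls an arm's mean change toward zero in proportion to its losses. The effect on the comparison depends on how losses fall between arms, so the rule cannot be relied on to be conservative. The inserted zeros are also treated as observed data when the standard error is computed.

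For the secondary outcomes, a child whose 3-month value is missing because of deterioration would be recorded as unchanged.

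**Working it through.** **The plan's own figures.** Inputs from section {14}: 60% on the routine formulation, and "It is estimated that the new method will increase the recovery rate by 30–40" per cent, read here as percentage points (90% to 100%), with alpha 0.05 (taken as two-sided) and power 80%. For 60% v 90%, pooled variance, no continuity correction:

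n = [1.96 × √(2 × 0.75 × 0.25) + 0.8416 × √(0.24 + 0.09)]² / 0.30² = (1.200 + 0.483)² / 0.09 = 31.5, so 32 per arm.

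The stated figure is 33, close enough to confirm the reading. Then 33 / 0.9 = 36.7, so 37 per arm and 74 in total. Planned loss is 37 − 33 = 4 per arm.

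**What the rule does.** With one value before treatment and one after, imputed change = baseline − baseline = 0. If a share m of an arm is missing and the lost children would have changed like the rest, the arm's expected mean change is (1 − m) × true change.

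**Assumptions for what follows.** The SD of change is set to 1. The true changes and the loss splits are illustrations, because the protocol article gives none. Means are compared by pooled t test, 37 per arm, 100,000 simulated trials.

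**Equal loss, 4 and 4.**
- Difference retained: 33/37 = 0.892, so 0.70 SD becomes 0.62 SD.
- Changes of 0.7 v 0 SD: power 79.6% against 80.0% in the 33 observed per arm; coverage 94.0% against 95.0%.
- Changes of 1.0 v 0.3 SD: power 78.7% against 80.0%; coverage 94.4% against 95.0%.
- Changes of 2.0 v 1.3 SD: power 71% against 80%.

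The last drop follows from the variance under the rule, (1 − m) + m(1 − m) × change², with m = 4/37. For 0.7 v 0 this is 0.939 and 0.892, so SE = √(1.831/37) = 0.222. For 2.0 v 1.3 it is 1.277 and 1.055, so SE = √(2.332/37) = 0.251. The observed-only SE is about 0.245 in both cases.

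**Unequal loss, no true difference, same gain g in both arms.** False difference = g × (a − b)/37, for a and b children lost.

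| Gain | Loss split | False difference | Two-sided error |
|---|---|---|---|
| 0.5 SD | 5/3 | 0.03 SD | about 5.0% |
| 0.5 SD | 6/2 | 0.05 SD | about 5.4% |
| 1 SD | 5/3 | 0.05 SD | about 4.4% |
| 1 SD | 6/2 | 0.11 SD | about 6.4% |
| 1 SD | 8/0 | 0.22 SD | about 14% |
| 2 SD | 6/2 | 0.22 SD | about 9% |

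**If recovery were analysed**, with every child deficient at baseline and 4 lost per arm counted as not recovered (exact enumeration, pooled two-proportion test, no continuity correction):
- 60% v 90%: 53.5% v 80.3%, so 30 points becomes 26.8. Power is 74% against 84% in the 33 observed per arm.
- 60% v 100%: 53.5% v 89.2%, so 40 points becomes 35.7. Power is 99.3% against 99.99%.

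**The case against.** The best defence is that little is lost in the plan's own base case. At 4 and 4 the test of means barely moves for changes up to 1 SD, equal loss works against the new formulation, and a 5/3 split does not raise the error rate above 5%. Monthly visits, phone calls and free-of-charge visits should keep losses low. This stands, and it is why the point is modest.

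The recovery figures are open to challenge too. Only the 60% v 90% case shows a sizeable loss of power. The calculation takes every child as deficient at baseline, whereas eligibility requires no deficiency, and a child sufficient at baseline would be carried forward as sufficient. Section {20a} names no between-group test of proportions. All of this stands, so the recovery figures are conditional.

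Three stronger readings are tempting but unsupported:
- **Every outcome is certainly affected.** This is secure only for serum vitamins. If BMI or the clinical score is recorded at the monthly visits, a later value could be carried. The text does not say so, and the schedule table is not shown.
- **The rule favours the nanomicelle arm.** Free drops once a day against four pills daily give a reason why losses might differ. The protocol article gives no rate for either arm.
- **Stopping treatment makes the 3-month value missing.** Section {11b} stops the intervention, not follow-up. Where the 3-month value is collected, the rule has no effect.

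**Conclusion.** The point holds for the primary outcome. Sections {12}, {13} and {20c} together turn each missing 3-month vitamin level into the baseline level. This is a stated rule, not a detail left to an analysis plan that is not shown. For the secondary outcomes it holds on the text as given, subject to what is recorded at the monthly visits. There, missingness through deterioration biases the comparison only if it differs between arms.

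The size is modest at the planned loss: a difference shrinks to 89%, with almost no loss of power for changes up to 1 SD. A reader might take the figures as worst cases. They are not: an 8/0 split, a 2 SD gain, or lost children who would have changed more than the others all give larger effects. Every figure except the planned loss of 4 and the 33/37 ratio rests on assumed changes and loss splits. The change is worth making because it is cheap and the present rule has no good justification with two measurement times.

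**What to change.** In section {20c}, replace carry-forward as the main method by one of:
- a baseline-adjusted analysis (ANCOVA) of the observed 3-month values, a technique that section {20a} already names for the secondary outcomes; or
- multiple imputation by arm using baseline values.

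Either is enough. With baseline as the only predictor, imputation adds little to the ANCOVA. Both assume that missing children resemble similar children who completed. Keep the carried-forward baseline only as a sensitivity analysis, and make the change before the data are analysed. If the timeline still allows, add that children who stop treatment are still assessed at 3 months unless consent is withdrawn. The trial status section reports recruitment complete on November 30, 2022 and procedures expected to end by April 2023, so this last step may come too late.

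The cost is a few sentences and slightly more analysis work. In the 0.7 v 0 SD example, intervals are about 10% wider before any gain from baseline adjustment (0.245/0.222 = 1.10). That is not a real loss of information, because the carried-forward interval is narrower there only through the inserted zeros.

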### Plans to give access to the full protocol, participant-level data, and statistical code {31c}

At the earliest opportunity, we will essay to release the full study protocol and results, irrespective of the magnitude or direction of the effect. The anonymized data set and statistical code may be available from the corresponding author (email: [contact]) on reasonable request.

## Oversight and monitoring

### Composition of the coordinating center and trial steering committee {5d}

Due to the low-risk intervention, the data monitoring committee was not involved in the current study. The trial is overseen by a diverse team of healthcare professionals, including gastrointestinal specialists, pulmonologists, nutritionists, and other experts. The blinded nutritionist, unaware of group assignments, maintains regular communication through weekly phone calls and monthly in-person visits, contributing to the ongoing success of the trial. Additionally, the Cystic Fibrosis Clinic actively participates in these regular sessions to monitor progress and maintain the trial’s steady momentum. However, all researchers are committed to reporting any adverse events.

### Composition of the data monitoring committee, its role and reporting structure {21a}

The establishment of a data monitoring committee (DMC) was deemed unnecessary for this particular study due to the low-risk nature of the intervention. The trial is being closely monitored by the ethics committee of Mashhad University of Medical Sciences (MUMS) as part of their oversight role throughout the trial. The ethics committee ensures adherence to ethical guidelines, patient safety, and the integrity of the trial, thereby ensuring the well-being and protection of participants.

